### Collection of milk and oropharyngeal administration procedure

Obstetric nurses will encourage the mother of each newborn to start lactation within 24 h of delivery and educate them on breast massage and electric breast suction every 3 h. Mothers of preterm infants will be encouraged to milk frequently with hygienic hands to ensure a steady supply of breast milk. To ensure the feasibility of oropharyngeal administration of mother’s milk to preterm infants in the treatment group, the mother’s milk will be collected in a pre-labeled sterile milk collection bag. A minimum colostrum volume of 1.6 ml will be collected and stored in the breast milk refrigerator of NICU. After ascertaining that baby's information is consistent with details in the label on the breast milk storage bag, an on-site investigator (nurses preparing syringes) will select the storage bag with the latest lactation time and use sterile gloves and syringes to suck 0.1 ml of colostrum or sterile water for oropharyngeal administration, and cover them with opaque tape and needle cap. Each syringe will be labeled with serial number, hospitalization number, name and date. Then, the bag will be stored at 0 ~ 4℃ for 24 h for subsequent intervention. In this study, all other storage bags will be stored in a freezer at -18 °C until the infant begins enteral feeding.

In the first 48–72 h the treatment group will receive the treatment measures: two 1 mL sterile syringes each aspirated with 0.1 mL of colostrum, placed at room temperature for 5 min. The colostrum will be maintained at room temperature for OAC use. After removing the tip and cap of the first syringe, the colostrum will be slowly injected along the right oral mucosa for at least 20 s. Then, the right buccal mucosa will be wiped with a sterile cotton swab for at least 10 s. The second syringe will be used in the same way on the left oral mucosa. The procedure will be performed every three hours for five days. The control group will be treated with sterile water following similar operation steps. Colostrum for the control group will be frozen in the NICU breast milk refrigerator for enteral feeding. Vital signs will be monitored throughout the process, including heart rate, respiration, body temperature and pulse oxygen saturation. During treatment, newborns will be regularly monitored and observed. If their clinical symptoms are unstable (heart rate is greater than 200 or less than 100, breathing is greater than 80, or the oxygen saturation is maintained above 85% only when the oxygen concentration increases by 10%) [44], the intervention will be interrupted. Once the clinical situation stabilizes, the treatment will be resumed immediately, and the final intervention dose and adverse reactions recorded.

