### Participant recruitment and informed consent

Data collection will begin in October 2022 and is expected to end in September 2023. Shenzhen People’s Hospital is the pilot research unit, and the pilot research will be carried out from August to September 2022. The annual census of very preterm infants in this facility is relatively high and the breastfeeding rate is very high (above 80%), hence ideal for the recruitment of subjects. Mothers who meet the inclusion criteria (fetal weight < 1500 g estimated by ultrasound) will be invited to participate. To achieve full registration of participants and target sample size, breast-feeding education will be provided in obstetrics to improve lactation awareness. Professional staff will guide pregnant women and provide them with breast care (such as breast massage). The principal investigator (PI) will explain the study in detail and respond to any questions raised. Mothers will be informed of their right to withdraw from the intervention at any time. They will also be informed that if they decline to participate in the study, their care and that of their infants will not be affected.

Written informed consent will be obtained from the patient's guardian. This study complies with the Declaration of Helsinki.

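### Milk storage is specified differently by arm and is not masked, so the NICU milk store can reveal allocation to staff who handle milk

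*Protocol article*

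**What the plan says.** The relevant sentences are all in the section on collection of milk and the oropharyngeal procedure.

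- **Collection.** Labelled bags are introduced to make feasible the "oropharyngeal administration of mother’s milk to preterm infants in the treatment group". The next sentence sets the minimum: "A minimum colostrum volume of 1.6 ml will be collected and stored in the breast milk refrigerator of NICU".
- **The bag in use.** The preparer takes the most recently expressed bag and draws up the syringes. "Then, the bag will be stored at 0 ~ 4℃ for 24 h for subsequent intervention".
- **Other bags.** With no mention of arm, "all other storage bags will be stored in a freezer at -18 °C until the infant begins enteral feeding".
- **Control milk.** "Colostrum for the control group will be frozen in the NICU breast milk refrigerator for enteral feeding".
- **Lactation support.** "Obstetric nurses will encourage the mother of each newborn to start lactation within 24 h of delivery", and "Mothers of preterm infants will be encouraged to milk frequently with hygienic hands to ensure a steady supply of breast milk". Neither sentence is limited to one arm.

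On blinding, the collection section has the syringes covered with opaque tape. The Randomization section separates the person who prepares the syringe from the nurse who gives it, and lists the subjects, the intervention nurses, the principal investigator and the data verifier as blinded. Nothing is said about masking the milk store or about who has access to it.

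**The concern.** Masking here is built around the syringe. The milk supply behind the syringe is left visible and, as written, differs by arm: an OAC infant has a chilled bag reserved for the next doses, and a control infant has frozen milk only. Anyone who fetches or sorts milk on the unit could read the allocation from that.

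What is at stake is equal care rather than outcome assessment. The Shannon index and short chain fatty acids come from sequencing and mass spectrometry, and knowledge of the arm would not readily distort those. But the Discussion names feeding type as a factor that shapes the gut microbiota. If staff who know the arm feed, or encourage expression, differently, a day-7 difference could partly reflect feeding instead of the 0.2 ml placed on the mucosa.

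**Working it through.** **The one figure that can be checked.** Dose 0.2 ml and interval 3 h (Study design).

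- Doses per day = 24 / 3 = 8.
- Daily volume = 8 × 0.2 ml = 1.6 ml, which reproduces the stated minimum.
- Over 5 days = 5 × 1.6 ml = 8 ml.

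So the minimum is one day's OAC supply. This supports reading it as a treatment-arm requirement, since sterile water needs no milk. It does not by itself show that mothers in the two arms are asked to do different things.

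**Storage, side by side.**

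| Milk | Stated storage | Arm stated? |
|---|---|---|
| Bag in use for oropharyngeal doses | 0–4 °C for 24 h | Implied OAC, as it is kept for later doses |
| All other bags | −18 °C until enteral feeding begins | No |
| Control colostrum | Frozen, for enteral feeding | Control |

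Two readings are possible.

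1. A bag is selected and chilled only for OAC infants. The sentence on control colostrum then fits, and storage differs by arm. A chilled bag marks OAC and its absence marks control.
2. A bag is selected and chilled in both arms. The preparer sentence allows this, because it describes choosing a bag and then drawing either colostrum or water. The cue would disappear, but this sits uneasily with the statement that control colostrum is frozen.

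The first reading weakens blinding; the second is in tension with the text. Either way the sentences need reconciling.

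**How long the cue lasts.** The bag is held for 24 h and dosing runs for 5 days, so under the first reading the cue can recur on each treatment day. It is clearest before enteral feeding starts. After that, the article does not say how feeding milk is stored in either arm.

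**Do existing measures remove it?** Opaque tape hides the syringe contents from the nurse giving the dose. A separate preparer hides the drawing-up. Neither hides the bag.

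**Would the analysis absorb a feeding difference?** Table 1 gives a t-test or Wilcoxon test for both primary outcomes. Adjustment for feeding type by redundancy analysis is conditional (Statistical analysis). Feeding type after randomisation could itself be affected by the arm, so adjusting for it would not cleanly remove such a difference. Data collection records feeding type but does not name whether the milk was chilled or frozen.

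The point changes no sample size, power or type I error figure.

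**The case against.** The strongest reply is that the text establishes a difference in storage and little else. Four stronger conclusions that a reader might draw do not hold.

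- **Mothers are unblinded.** The milk is kept in the NICU. No sentence has mothers seeing the store or being told different things by arm.
- **Lactation effort differs by arm.** The encouragement and the three-hourly expression advice go to every mother, and breast-feeding education under Participant recruitment is not arm-specific. There is an incentive: the Missing data section counts an infant as lost if less than 70% of the intended dose is given, and lack of milk can cause that only in the OAC arm. It also lists lactation encouragement as a means of retention. But extra prompting of OAC mothers remains an inference. What can be said is that the scope of the 1.6 ml minimum is unclear.
- **The milk fed differs by arm.** Bags not in use are frozen until feeding in both arms, and nothing says that the chilled remainder of an OAC bag is fed.
- **Up to 20% of mothers could not meet the minimum.** The rate above 80% is the breastfeeding rate at one hospital, the pilot unit. It is not the share of enrolled mothers able to express 1.6 ml in a day.

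It can also be said that the syringes are masked, the outcomes are laboratory measures, feeding is recorded, and access to the milk store is a detail that an article may leave to the full protocol. The first three limit the harm, and the access detail is rightly not counted as missing. What stands is that the article does state a storage rule, and the rule differs by arm. That is a feature of the stated design and not an omission.

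**Conclusion.** The point holds in a limited form. As written, milk storage differs by arm with no masking or matching, so the milk store can reveal allocation to NICU staff who handle milk. The sentence about drawing colostrum or water sits uneasily with the one about freezing control colostrum, and the scope of the 1.6 ml minimum is ambiguous.

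The conclusion assumes that the chilled bag is kept for OAC infants only and that some staff beyond the preparer can see the store; the article does not settle either. Any bias would come through feeding and other care. Its size cannot be computed: the article gives no enteral volumes, no number of staff with access, and no arm difference in feeding. The 1.6 ml per day and 8 ml in total describe the intervention and do not measure bias.

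The change is worth making because it is cheap and protects a blinding claim that the trial relies on.

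**What to change.** Reconcile the sentences on collection and storage so that they describe one milk pathway for both arms, under whatever storage rule the clinical team sets. The text should say that collection, the 1.6 ml minimum, the daily setting aside of a bag, its storage and the handling of the remainder are the same for every infant. If they cannot be the same, it should say how storage is masked from staff other than the preparer. Clarify whether a bag is handled in both arms when syringes are prepared. State that any lactation prompts apply to all mothers regardless of arm.

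No check of milk availability before randomisation is needed for this purpose. It would act as a new eligibility condition and change the population.

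The cost is wording in the protocol and nursing procedure, and slightly more milk handling and refrigerator space for control infants. Because the Trial status section says that recruitment is under way, the change would be an amendment, and its date should be recorded so that infants treated before and after it can be told apart.

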## Outcomes

Primary outcome measures: 1a) a between-group difference in gut microbial alpha diversity will be measured using Shannon diversity index at the 7th day and 1b) a between-group difference in the concentration of fecal metabolites (short chain fatty acids) will be quantitatively measured using non-targeted liquid chromatography-mass spectrometry (LC–MS) at the 7th day.

Secondary outcome measures: 2a) between-group differences in other diversity indicators of gut microbiota, including Simpson index (an indicator of species richness and evenness less affected by rare species than Shannon index) and Chao1 index (estimated total number of species) at the 7th day; 2b) between-group differences in alpha diversity of gut microbiota measured using Shannon index, Simpson index and Chao1 index on the 14th, 21st and 28th days of life; 2c) Between-group differences in the concentration of fecal metabolites quantitatively measured by non-targeted LC–MS at the 14th, 21st and 28th days of life; 2d) proportion of gut microbiota at phylum and genus level; 2e) gut microbial beta diversity explaining between-sample dissimilarity calculated using the Vegan package; and 2f) correlation between the comparative dominant flora and metabolites (Table 1).

**Table 1 Tab1:** Outcomes, measures and methods of analysis

Outcome	Hypothesis	Outcome Measure	Methods of Analysis
**1.Primary** 1a A between-group difference in Shannon diversity index at the 7th day	OAC increases Shannon diversity and metabolites of gut microbiota	Shannon index (continuous)	Individuals: Wilcoxon text; Intergroup: T/Wilcoxon text
1b A between-group difference in fecal metabolites at the 7th day		Short chain fatty acids (continuous)	Individuals: FC, PCA/PLS-DA Intergroup: T/Wilcoxon text
2.** Secondary** 2a Between-group differences in other alpha diversity indexes (Simpson, Chao1) at the 7th day	OAC increases other alpha diversity and beta diversity, and changed the proportion of gut microbiota from birth to day 28. There is a Correlation between dominant microbiota and metabolites	Simpson index, Chao1 index (continuous)	Individuals: Wilcoxon text; Intergroup: T/Wilcoxon text
2b Between-group differences in Shannon index, Simpson index and Chao1 index at the 14th, 21st and 28th days of life		Shannon index, Simpson index, Chao1 index (continuous)	Individuals: Wilcoxon text; Intergroup: T/Wilcoxon text
2c Between-group differences in the concentration of fecal metabolites at the 14th, 21st and 28th days of life		Short chain fatty acids (continuous)	Individuals: FC, PCA/PLS-DA Intergroup: T/Wilcoxon text
2d Proportion of gut microbiota (phylum and genus level)		The percentile of gut microbiota at the phylum and genus levels of the total microbiota (binary)	Individuals: Wilcoxon text; Intergroup: Chi-square test
2e Gut microbial beta diversity		Bray–Curtis distances with 9999 permutations (continuous)	PCOA; LDA
2f Correlation between dominant microbiota and metabolites		Correlation between dominant microbiota and metabolites	Partial Least Squares Discriminant Analysis

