### Statistical analysis

Intention to treat (ITT) method will be used for statistical analysis. Baseline maternal and infant demographic and clinical characteristics of OAC group and placebo group will be compared using chi-square or Fisher’s exact test (such as infant sex, mode of delivery and presence or absence of chorioamnionitis) and t-test or Wilcoxon test for continuous variables. After removing low-quality sequences, original data will be analyzed following the steps of 16S rRNA discovery, clustering and identification. The number of operational taxonomic units (OTUs) will be calculated for each sample at a 97% sequence similarity level. A specific taxonomic unit will represent a specific species. Subsequently, a sparse curve will be drawn based on the results of OTUs generated using sample sequencing. Wilcoxon test will be used to analyze the diversity and richness of microbiota within individuals. A t-test or Wilcoxon test will be used to compare alpha diversity (Shannon index, Simpson index, and Chao1 index) between the two groups of infants with and without OAC intervention within four weeks of birth. Repeated measures analysis of variance (ANOVA) (for normally distributed data) or Kruskal Wallis test (for non-normal data) will be used to evaluate the microbial alpha diversity at different time points. The proportion difference of gut microbiota at the phylum and genus levels will be calculated using chi-square or Fisher's exact test. Values with *p* < 0.05 will be considered statistically significant. Beta diversity will be calculated using the Vegan package, and a principal co-ordinates analysis (PCOA) based on Bray–Curtis distances will be plotted. Adonis permutational multivariate analysis of variance of Bray–Curtis distances with 9999 permutations will be used to compare microbial community structure between each of the two groups.

Redundancy analysis (RDA) will be performed using the Vegan package to define the factors that could significantly affect gut microbial composition in each group. We will use Linear discriminant analysis (LDA) of effect size (LEfSe) to determine the most discriminant taxa between the two groups. If the effect of OAC intervention on gut microbiota is less than that of other confounding factors (delivery mode, antibiotic use, feeding type, etc.), we will adjust it with RDA.

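### Table 1 predicts that OAC increases beta diversity, but no named analysis tests whether dissimilarity rises; Adonis tests only whether composition differs between arms

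*Protocol article*

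**What the plan says.** - **Hypothesis.** In the Outcomes section, the Table 1 hypothesis entry for the secondary outcomes reads "OAC increases other alpha diversity and beta diversity, and changed the proportion of gut microbiota from birth to day 28". For beta diversity this is directional.
- **Outcome.** The Outcomes text defines 2e as "gut microbial beta diversity explaining between-sample dissimilarity calculated using the Vegan package". The measure in Table 1 is Bray–Curtis distance, labelled continuous.
- **Methods in Table 1, row 2e.** Only PCOA and LDA are listed. The 9999 permutations appear in the measure column, without the test they belong to.
- **Methods in Statistical analysis.** The PCOA is to be plotted. LEfSe is used "to determine the most discriminant taxa between the two groups". The one inferential test for beta diversity is "Adonis permutational multivariate analysis of variance of Bray–Curtis distances with 9999 permutations", which "will be used to compare microbial community structure between each of the two groups". The section then refers to Table 1 for the details of all methods.

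**The concern.** The hypothesis concerns an amount: whether samples are more dissimilar under OAC than under sterile water. The named test concerns a different quantity: whether the two arms have the same community composition. A trial can show either one without the other.

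If a significant Adonis result were set against the Table 1 hypothesis, it could be reported as support for increased beta diversity when dissimilarity was equal or lower under OAC. A true increase could also go unreported because nothing in the plan measures it. Both can be avoided by settling now which question 2e asks.

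**Working it through.** **1. Sample size used for the check.** The article states no figure for beta diversity, so the check uses the evaluable number per arm from the Sample size section (Shannon difference 0.2, SD 0.6, two-sided 0.05, power 80%).

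n = 2(z₀.₉₇₅ + z₀.₈₀)²σ²/δ² = 2(1.960 + 0.842)² × 0.36/0.04 = 141.3, rounded up to 142. The t-test version gives 142.2, rounded up to 143. The stated 143 per arm is reproduced.

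**2. What the Adonis statistic contains.** Let V₁ and V₂ be the mean squared distances within the OAC and control arms, C the mean squared distance across arms, and n the number per arm.

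- Within-group sum of squares: (n − 1)/2 × (V₁ + V₂) = 71(V₁ + V₂)
- Between-group sum of squares: (n/2)C − (n − 1)/4 × (V₁ + V₂) = 71.5C − 35.5(V₁ + V₂)
- Pseudo-F: between-group sum of squares ÷ (within-group sum of squares/284)

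The hypothesis is about V₁ against V₂. With equal arms only their sum enters, so exchanging the arms leaves F and its permutation p-value unchanged. The test therefore has no direction. This needs no assumption about the community.

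**3. Rejection with no change in dissimilarity.** Bray–Curtis is unaffected by relabelling taxa. If the OAC arm has the control arm's distribution with some taxa exchanged, within-arm dissimilarity is identical in both arms while composition differs. Adonis should detect that difference, but it is not an increase in beta diversity.

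**4. Illustrative rates.** Assumptions: 40 taxa with mean shares proportional to 0.75ᵏ, Dirichlet-multinomial counts, 5,000 reads, 143 per arm, 200 trials per scenario and 299 permutations. The dispersion test is a t-test on distances to the group centroid. Simulation error is at most √(0.25/200), about 3.5 points. In the swapped scenarios three adjacent pairs of taxa are exchanged; the largest exchange is between shares of 0.25 and 0.1875.

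| Scenario | Mean within-arm Bray–Curtis, OAC / control | Adonis rejects | Dispersion test rejects |
|---|---|---|---|
| No difference | 0.601 / 0.601 | 4% | 7% |
| Taxa swapped, equal dispersion | 0.601 / 0.602 | 98% | 7% |
| Taxa swapped, OAC less dispersed | 0.553 / 0.602 | 100% | 91%, always OAC lower |
| Same mean, OAC more dispersed | 0.618 / 0.601 | 8.5% | 21% |
| Same mean, OAC more dispersed | 0.635 / 0.601 | 8% | 57% |
| Same mean, OAC more dispersed | 0.655 / 0.602 | 16% | 89% |
| Same mean, OAC more dispersed | 0.702 / 0.602 | 95.5% | 100% |

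**5. Sensitivity to the assumed community.** Logistic-normal communities give the same pattern. For a rise of about 0.025, Adonis rejects in 4–11% and the dispersion test in 55–84%. For a rise of about 0.05, the figures are 25–51% and 98–100%. In other Dirichlet runs with control dissimilarity near 0.66, Adonis rejected in 70–87% of trials when OAC lowered dissimilarity by 0.03 to 0.04.

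**The case against.** The strongest defence is that the article does not misuse Adonis. The Statistical analysis section assigns it to comparing community structure, which is what it does. The rejections in the swapped scenarios are correct detections of a real compositional difference, and no sentence says that a significant result will be read as an increase. A reader might infer that Adonis is the wrong test, or that it has an inflated error rate; the document does not support that. This part of the defence stands.

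A reader might also infer that Adonis generally misses a real increase. That too goes beyond the evidence. The low rates need mean composition to be nearly equal, whereas the Background and Data collection sections predict compositional shifts. In one set of runs with dissimilarity rising from 0.56 to 0.60, Adonis rejected in 10% of trials with identical means, 62% with an opposite 3-point shift in two taxa, and 100% with a 6-point shift. A large pure increase is also detected. In none of these cases does the result carry a direction.

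Three further points have weight:
- The stated aim in the Background is non-directional, and between-sample dissimilarity need not mean dissimilarity within an arm. The conflict may come down to one verb. If so, that verb is wrong and should change.
- The expected dominance of Lactobacillus/Bifidobacterium does not establish that infants become more alike, since different genera could dominate in different infants. A fall in dissimilarity is possible, not predicted.
- A dispersion check beside Adonis is a detail that a full analysis plan could hold. The conflict between the stated hypothesis and the stated methods is nevertheless in the article itself.

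**Conclusion.** The mismatch holds. Table 1 states a directional hypothesis about the amount of dissimilarity, and no named analysis estimates or tests it. A significant Adonis result can support a difference in composition but not an increase in beta diversity. A non-significant result does not rule out a moderate increase when mean composition is nearly the same in both arms.

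The absence of direction follows from the form of the statistic and does not depend on the simulations. The percentages do depend on assumed communities, because the article gives no community profile, no within-arm Bray–Curtis value and no expected dispersion effect. They are illustrative. The dispersion comparator rejected in about 7% of null trials in the Dirichlet runs, so its power is slightly flattered, though by far less than the gaps seen for moderate increases.

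The effect is confined to one secondary outcome. The primary endpoints and the sample size are unaffected. It should be corrected because a wrong directional claim is easy to prevent.

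**What to change.** Choose one question for 2e and make Table 1 agree with it.

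1. **If an increase is meant:** keep the directional hypothesis and test it with a dispersion test on the same Bray–Curtis matrix (betadisper with permutest, in the Vegan package already named). Report mean within-arm dissimilarity for each arm, with the difference and its confidence interval. Keep Adonis for a separate, non-directional hypothesis about composition, listed as such.
2. **If a compositional difference is meant:** reword the beta-diversity part of the Table 1 hypothesis to say that OAC changes community composition, and list Adonis as the test in row 2e.

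The cost is one reworded hypothesis, or one extra analysis in the same software with a short addition to the table. No new data and no change in sample size are needed.
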